# Terminologies and Abbreviations

| ACE | Angiotensin Converting Enzyme |
| --- | --- |
| ACG | American College of Gastroenterology |
| AGEP | Acute Generalized Exanthematous Pustulosis |
| ALB | Albumin |
| ALP | Alkaline Phosphatase |
| ALT | Alanine Aminotransferase |
| AST | Aspartate Aminotransferase |
| BUN | Blood Urea Nitrogen |
| CABG | Coronary Artery Bypass Graft |
| CBC | Complete Blood Count |
| COX | Cyclo-Oxygenase |
| CPK | Creatine Phosphokinase |
| CRC | Clinical Research Coordinator |
| CRF | Case Report Form |
| CRO | Contract Research Organization |
| CTCAE | Common Terminology Criteria for Adverse Events |
| CYP | Cytochrome |
| DBP | Diastolic Blood Pressure |
| DRESS | Drug Rash with Eosinophilia and Systemic Symptom |
| DSMB | Data and Safety Monitoring Board |
| ECL | Enterochromaffin-Like |
| ELISA | Enzyme-Linked Immunosorbent Assay |
| FAS | Full Analysis Set |
| GCP | Good Clinical Practice |
| GFR | Glomerular Filtration Rate |
| γ-GT | Gamma Glutamyltransferase |
| GSRS | Gastrointestinal Symptom Rating Scale |
| Hb | Hemoglobulin |
| HCV | Hepatitis C Virus |
| HR | Heart Rate |
| ICH | International Conference on Harmonisation of Technical Requirements for Registration of Pharmaceuticals for Human Use |
| IND | Investigational New Drug |
| ITT | Intent-To-Treat |
| KGCP | Korean Good Clinical Practice |
| LDA | Low Dose Aspirin |
| LDH | Lactate Dehydrogenase |

| LDQ | Leeds Digestion Questionnaire |
| --- | --- |
| MCD | Minimal Change Disease |
| MCID | Minimal Clinically Important Difference |
| MCTD | Mixed Connective Tissue Disease |
| MedDRA | Medical Dictionary for Regulatory Activities |
| MRI | Magnetic Resonance Imaging |
| NPN | Non-Protein Nitrogen |
| PLT | Platelet |
| PR | Pulse Rate |
| PPI | Proton Pump Inhibitor |
| PTT | Partial Thromboplastin Time |
| PT | Preferred Term |
| RBC | Red Blood Cell |
| SAE | Serious Adverse Event |
| SLE | Systemic Lupus Erythematosus |
| SOC | System Organ Class |
| SODA | Severity of Dyspepsia Assessment |
| SUSAR | Suspected Unexpected Serious Adverse Reaction |
| TEN | Toxic Epidermal Necrolysis |
| UNL | Upper Normal Limit |
| VAS | Visual Analogue Scale |
| WBC | White Blood Cell |
| WHO | World Health Organization |
| WHOART | WHO Adverse Reactions Terminology |

# Synopsis

| Trial Title | A prospective, randomized, double-blind, double-placebo, active-controlled, multicenter, interventional study to compare the gastroprotective and pain-relieving effects of Naxozol and celecoxib in patients with osteoarthritis | | |
| --- | --- | --- | --- |
| Trial Number | Naxozol_P4_1 | Version | 1 |
| Sponsor | [name] (Severance Hospital, Department of Orthopedics) | | |
| Phase | Phase 4 (investigator-initiated trial) | | |
| IND | Applicable [figure not shown] Not applicable | | |
| Institutions / Countries | 10 institutions / Korea | | |
| Expected duration of study | Approximately 24 months after study initiation | | |
| Purpose | **Primary Purpose**  To prove non-inferiority of the gastroprotective effect of a 12-week administration of Naxozol to osteoarthritis patients compared to that of celecoxib, as evaluated by the Leeds Dyspepsia Questionnaire (LDQ).  **Secondary Purpose**   - To compare the gastroprotective effect, as evaluated by the Gastrointestinal Symptom Rating Scale (GSRS), of 12 weeks of treatment of osteoarthritis patients with Naxozol or celecoxib. - To compare the incidence rate of gastrointestinal (GI) adverse events, as well as the drug discontinuation rate due to gastrointestinal (GI) adverse events, after 12 weeks of treatment of osteoarthritis patients with Naxozol or celecoxib. - To compare the pain improvement effect, as evaluated by the visual analogue scale (VAS), of 12 weeks of treatment of osteoarthritis patients with Naxozol or celecoxib. - To compare the improvement in quality of life (QoL), as evaluated by EQ-5D, of 12 weeks of treatment of osteoarthritis patients with Naxozol or celecoxib. - To compare patient compliance during 12 weeks of treatment of osteoarthritis patients with Naxozol or celecoxib. - To compare overall safety of Naxozol and celecoxib after 12 weeks of treatment of osteoarthritis patients. | | |
|  |  |  |  |
|  |  |  |  |

| Planned study design | Prospective, randomized, double-blind, double-placebo, active-controlled, two-arm, parallel, multi-center trial. |
| --- | --- |
| Expected number of study subjects | A minimum of 106 (53 in experimental group, 53 in control group), considering a 20% discontinuation rate, with the final aim of 42 subjects in each of the two groups. |
| Visit schedule and evaluation | Screening & washout period: ~14 days (Day -14 to Day 1 [Week -2 to 0]).  Treatment and F/U period: 12 weeks (Day 1 to Day 84 [Week 12]).  **Visit Schedule for Evaluation**  Visit 1: screening & washout, Day -14 to Day 1.  Visit 2: randomization, Day 1.  Visit 3: end of study, Day 84±7 from date of randomization.  **Schedule for Evaluation**  **1) Safety and tolerability evaluation**  Adverse events, physical examination, vital signs, laboratory tests (hematological test, blood chemistry), co-administered drugs.  Adverse events: V1-V3, at every visit.  Co-administered drugs: V1-V3, at every visit.  Vital signs (VS): at V1 and V3.  Physical examination: at V1 and V3.  Laboratory tests:  - Hematological test: at V1 and V3.  - Blood chemistry: at V1 and V3. |
| Inclusion criteria | 1. Subjects of Korean nationality who voluntarily decide to participate in the study after receiving and understanding a detailed explanation of the study and provide written consent. 2. Men and women who are ≥50 years old at the time of consent. 3. Persons who are available for follow-up for the duration of the study and who are able to perform tasks for the study, such as reading and filling out EQ-5D and VAS surveys. 4. Persons with a confirmed medical history of physically symptomatic osteoarthritis who score ≥40 mm on pain VAS performed at V2. 5. Persons deemed appropriate for the study based on the screening results (N.B.: subjects can be included at the discretion of the investigator even if laboratory test results are outside reference ranges). |
| Exclusion criteria | 1. Persons who are participating in a clinical study or have participated in a clinical study <30 days prior (participation is based on the date of final investigational product administration). 2. Persons with a history of abuse of alcohol or other drugs <6 months prior to screening. 3. Persons who drink 21 standard drinks or more per week (generally, 55 mL soju is equated to 200 mL beer or 30 mL spirits). 4. Persons with a history of peptic ulcer disease with complications (bleeding, perforation, penetration, and gastric outlet obstruction) within the last 5 years. 5. Persons with a history of peptic ulcer disease without complications within 6 months prior to screening visit or persons with active peptic ulcer disease. 6. Persons who have been infected with *Helicobacter* but did not undergo eradication therapy. 7. Persons with a known history of gastroesophageal reflux disease. 8. Persons with a confirmed diagnosis or clinical suspicion of the following arthropathies that may affect safety and efficacy evaluation: septic arthritis, inflammatory arthropathy such as rheumatoid arthritis, gout, recurrent pseudopain, Paget’s disease, fracture, ochronosis, acromegaly, hemochromatosis, Wilson’s disease, primary osteomalacia, and Ehlers Danlos Syndrome and other genetic collagen disorders. 9. Persons with surgery planned during the study period. 10. Persons with a history of gastrointestinal cancer. 11. Persons with a GI disorder due to drug absorption malfunction. 12. Persons with gastrointestinal bleeding, cerebrovascular bleeding, other bleeding disorders, or severe hematological disorders. 13. Persons with moderate to severe hepatic impairment (Child Pugh Class II or higher). 14. Persons with a history of severe heart failure or coronary artery bypass graft (CABG). 15. Persons with severe renal impairment (CrCl <30 mL / min). 16. Persons with severe hypertension (SBP ≥160 mmHg or DBP ≥100 mmHg) refractory to treatment. 17. Persons with a history of allergy to components of the investigational product. 18. Persons with hypersensitivity or allergy to other NSAIDs or PPI. 19. Subjects who received a contraindicated drug or therapy within a pre-specified period prior to study participation (Section 5.3.2). 20. Patients who are receiving a contraindicated co-administration drug (Section 5.3.3). 21. Patients who have a history of surgery on the osteoarthritic joint within the past year. 22. Women who are pregnant or breastfeeding, or women of childbearing age who are not using appropriate contraception (condom, diaphragm, intrauterine contraceptive device, or hormonal contraceptive drug used from ≥21 days prior to investigational product administration, or male vasectomy); this clause does not apply to menopausal women. 23. Persons deemed inappropriate for study enrollment by the investigator due to clinically relevant medical or psychiatric conditions. |
| **Experimental Drug** | Naxozol tablet: combination (naproxen 500 mg + esomeprazole 20 mg).  Dosage and administration: 1 tablet, twice daily. Do not split, chew, or crush tablet. Take 30 - 60 minutes before meal.  *Experimental group: Administer 1 Naxozol tablet 30 - 60 minutes before breakfast and 1 Naxozol tablet with 1 Celebrex placebo capsule 30 - 60 minutes before dinner. |
| **Control Drug** | Celebrex capsule: celecoxib 200 mg.  Dosage and administration: 1 capsule, once daily. Do not split, chew, or crush tablet. Take 30 - 60 minutes before meal (approved dosage and administration: 1 capsule, once daily, regardless of meal time).  *Control group: Administer 1 Naxozol placebo tablet 30 - 60 minutes before breakfast and 1 Naxozol placebo tablet with 1 Celebrex capsule 30 - 60 minutes before dinner. |
| **Planned Duration of Study** | 12 weeks total per subject. |
| **Primary outcome** | Average change in the Leeds Dyspepsia Questionnaire (LDQ) from baseline after 12 weeks of oral administration of investigational product. |
| **Secondary outcomes** | - Average change in the Leeds Dyspepsia Questionnaire (LDQ) from baseline after 12 weeks of oral administration of the investigational product. - Average change in the Gastrointestinal Symptom Rating Scale (GSRS) from baseline after 12 weeks of oral administration of the investigational product. - The incidence rate of GI adverse events (dyspepsia, diarrhea, nausea, abdominal pain, heartburn) after 12 weeks of oral administration of the investigational product. - The discontinuation rate due to GI adverse events after 12 weeks of oral administration of the investigational product. - Average change in the pain Visual Analogue Scale (VAS) from baseline after 12 weeks of oral administration of the investigational product. - Average change in the average EQ-5D score from baseline after 12 weeks of oral administration of the investigational product. - Drug compliance during 12 weeks of oral administration of the investigational product. - Ancillary and rescue drug use during 12 weeks of oral administration of the investigational product: average number of days used; average daily amount used (total amount used / total number of days used); and average amount of use during study participation (total amount used / study duration). - The incidence, frequency, and characteristics (clinical presentation, severity, result, etc) of adverse events during 12 weeks of oral administration of the investigational product. - Results of physical examination, vital signs, and radiological tests after 12 weeks of oral administration of the investigational product. |
| **Data analysis** | Definition of the analysis groups   - Safety evaluation group: subject group in which safety follow-up was performed at least once after randomization and investigational product administration. - FAS evaluation group: subject group in which efficacy evaluation was performed at least once after randomization and investigational product administration. - Per Protocol(PP) evaluation group: subject group in which efficacy evaluation was performed at least once after randomization and investigational product administration, with no major protocol violation.   Statistical analysis   - FA group (Modified ITT) and PP group are both considered the main analysis groups according to ICH recommendations, as this is a non-inferiority study. - If missing data occur during the study, they are substituted using the multiple imputation method. - To prove non-inferiority of the experimental drug, the one-sided 97.5% confidence interval for the difference in change in LDQ at 12 weeks compared to baseline between the two groups is obtained. If the 97.5% upper confidence limit is less than the pre-specified non-inferiority margin of 0.40, the null hypothesis is rejected, and non-inferiority is proven. - All statistical analyses, except the non-inferiority analysis, are fundamentally based on the two-sided test with an alpha level of 0.05. - No interim analysis is to be performed. - The mean, standard deviation, median, minimum and maximum values for continuous variables, and frequency and proportion for categorical variables, must be presented on principle, and the incidence frequency is presented if necessary.   The change between each time of measurement, or from the baseline of demographical and other baseline data, safety data, and efficacy data, are summarized in descriptive statistical values by treatment group. Additionally, normal / abnormal changes in physical examination and laboratory test results are shown in partition tables by treatment group.  Co-administered drugs are recorded in ATC terminologies, and adverse events are standardized to system organ class (SOC) or preferred term (PT) using a medical dictionary (MedDRA or WHOART). |

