## Discussion of the risk-benefit of the administration of the investigational product

This study is a phase 4 clinical study on osteoarthritis patients requiring NSAID administration.

The investigational product, the Naxozol tablet, is a slow-release tablet that contains naproxen, an NSAID, and esomeprazole, a PPI.

The clinical efficacy of NSAIDs in pain control in osteoarthritis patients is well accepted. Naproxen, an NSAID, and esomeprazole, a PPI, are both widely used and are safe drugs for pain improvement in osteoarthritis patients and for treatment of gastrointestinal bleeding or symptoms of dyspepsia associated with NSAID use, respectively.

The American College of Gastroenterology (ACG) guideline also recommends co-administration of PPI with NSAID use in patients with a moderate risk of gastrointestinal bleeding. (10)

Furthermore, in conducting this study, the contraindications for the investigational product have already been reflected in the inclusion / exclusion criteria, ensuring exclusion of high risk groups from the study.

In conclusion, a 12-week administration of Naxozol to osteoarthritis patients would not greatly increase the risk of harm to subjects if preceded by appropriate subject selection and followed-up by monitoring of adverse events. The safety of a 12-week oral administration within the given dose range is expected to be satisfactory with careful monitoring of adverse events and vital signs.

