## Warnings for use of the experimental drug

Warnings for use of the experimental drug are as follows:

1. If a patient who regularly drinks 3 or more standard drinks / day requires this drug or another antipyretic analgesic agent, a physician or pharmacist must be consulted. Such a person may be at an increased risk of gastrointestinal bleeding.
2. Cardiovascular risk: Use of NSAIDs, including this drug, may increase the risk of major cardiovascular events, myocardial infarction, and stroke, all of which can be fatal. This risk can increase with increasing duration of administration, and may be increased in patients with pre-existing cardiovascular disease or risk factors. The physician and patient must both carefully monitor for symptoms of such cardiovascular events, even without a history of cardiovascular disease. The patient must be aware of signs and / or symptoms of major cardiovascular toxicity and the appropriate response to take should such symptoms occur.
3. Gastrointestinal risk: Use of NSAIDs, including this drug, can increase the risk of gastrointestinal adverse events, including gastrointestinal bleeding, ulcers, or perforation, all of which can be fatal. This drug significantly reduced the incidence of GI ulcers compared to naproxen alone, but ulcers and their complications may still occur. Such adverse events can occur without warning symptoms during treatment. Elderly patients may be at an increased risk of such serious GI adverse events. A longer duration of treatment can increase the risk of GI adverse events, but short-term administration does not rule out such risks. Patients must be carefully monitored for signs or symptoms of GI ulcers or bleeding while on this drug. If serious GI adverse events are suspected, immediately perform additional assessments and provide treatment. It may be necessary to discontinue NSAID use until there is a complete resolution of serious GI adverse events. In high-risk groups, alternative treatments that are not related to NSAIDs should be considered.

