10. Anaphylactoid reactions: As with NSAIDs in general, anaphylactoid reactions have occurred in patients without known prior exposure to this drug. This complex symptom typically occurs in asthmatic patients who experience rhinitis with or without nasal polyps, or who exhibit severe, potentially fatal bronchospasm after taking aspirin or other NSAIDs. Emergency help should be sought in cases in which an anaphylactoid reaction occurs.
11. Skin reaction: This drug is a sulfonamide and can cause serious skin adverse events such as exfoliative dermatitis, Stevens-Johnson syndrome (SJS), and toxic epidermal necrolysis (TEN), which can be fatal. These serious events can occur without warning and in patients without prior known sulfa allergy. In most cases, such adverse events occur within 1 month of initiation of therapy with this drug. Patients should be informed about the signs and symptoms of serious skin manifestations and use of the drug should be discontinued at the first appearance of bullae, fever, skin rash or any other sign of hypersensitivity.
12. Patients with asthma may have aspirin-sensitive asthma. The use of aspirin in patients with aspirin-sensitive asthma has been associated with severe bronchospasm, which can be fatal. Since cross reactivity, including bronchospasm, between aspirin and other nonsteroidal anti-inflammatory drugs has been reported in such aspirin-sensitive patients, this drug should not be administered to patients with this form of aspirin sensitivity and should be used with caution in patients with preexisting asthma.
13. This drug cannot be expected to substitute for corticosteroids or to treat corticosteroid insufficiency. Abrupt discontinuation of corticosteroids may lead to exacerbation of corticosteroid-responsive illness. Patients on prolonged corticosteroid therapy should have their therapy tapered slowly if a decision is made to discontinue corticosteroids.
14. Based on pharmacological properties of this drug, signs and symptoms of fever or inflammation may be subdued, delaying the diagnosis of infectious complication under conditions of pain or non-infection.
15. If a patient shows signs of severe dehydration, fluid replacement must be given before administration of this drug, and patient must be monitored carefully.
16. This drug can be used on a short-term basis (within 1 week) for alleviation of acute pain (perioperative or post-extraction pain) in adults.

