#### Visit 2: Randomization visit (Day 1)

Visit 2 will be conducted on Day 1. The investigator will conduct the following procedures and evaluations for each subject:

- - Reconfirm the fulfillment of inclusion / exclusion criteria.
  - Conduct the pain VAS evaluation.
  - Conduct the LDQ evaluation.
  - Randomization.
  - Record all new adverse events and / or changes in pre-existing adverse events.
  - Record all co-administered drugs and / or changes in pre-existing co-administered drugs.
  - Distribute the GSRS and EQ-5D surveys and ask the subjects to answer them.
  - Distribute the investigational products.
  - Explain how to use the ancillary and rescue drugs, and how to fill out the subject log.
  - Distribute the ancillary and rescue drugs.
  - Confirm subject log completion and remind to bring the log at visit 3.
  - Book visit 3: the visit should be 84 days after visit 2 (Day 84 - 87).
  - Fill out the case report form.

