#### Reporting and evaluation of adverse events

At each visit, the subject will be asked about their health status. During the adverse event reporting period of the study, all undesirable status changes reported by the subject or observed by the investigator will be recorded as adverse events. All information regarding all adverse events experienced by a subject during the adverse event reporting period (stated below) will be recorded consistently, completely, accurately, and continuously in case report form. SAEs will be recorded additionally in the SAE report form, as per Section 6.3.1.1.4, and reported separately. For each adverse event, the description, duration (including date of occurrence and date of resolution: the timing must also be known if the timing of the adverse event incidence relative to the investigational product administration time is also important), seriousness, association with the study treatment, other suspected causes, treatment given, other treatments (including investigational product dose adjustment and discontinuation), and progress will be reported. SAEs must be strictly identified during the study period and recorded and reported according to the appropriate category.

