#### Thank you for taking the time to answer the questions above.

## Appendix 4. Subject log

| Protocol number | Screening number | | | | Randomization number | | | | Subject initials | | | | |
| --- | --- | --- | --- | --- | --- | --- | --- | --- | --- | --- | --- | --- | --- |
| Naxozol_P4_1 | S |  |  |  | R |  |  |  |  |  |  |  |  |

If you have taken the ancillary drug (Hanmi Almagate 500 mg tablet) or the rescue drug (Hanmi Susphen ER 650 mg tablet), please fill in the form below.

| **Date administered**  (e.g.: 2014 July 10  = **1 4 0 7 1 0**  Please enter one number per box). | | | | | | | **ⓛ Ancillary drug** | **② Rescue drug** |
| --- | --- | --- | --- | --- | --- | --- | --- | --- |
|  |  |  |  |  |  |  | **Hanmi Almagate 500 mg tablet**  [figure not shown] | **Susphen ER 650 mg tablet**  [figure not shown] |
|  |  |  |  |  |  |  | Take if gastrointestinal dysfunction is severe beyond toleration. Do not exceed 6 tablets per day. | Take if pain is severe beyond toleration. Do not exceed 4 tablets per day. |
| 1 |  |  |  |  |  |  | Tablets | Tablets |
|  | Y | Y | M | M | D | D |  |  |
| 2 |  |  |  |  |  |  | Tablets | Tablets |
|  | YY MM DD | | | | | |  |  |
| 3 |  |  |  |  |  |  | Tablets | Tablets |
|  | YY MM DD | | | | | |  |  |
| 4 |  |  |  |  |  |  | Tablets | Tablets |
|  | YY MM DD | | | | | |  |  |
| 5 |  |  |  |  |  |  | Tablets | Tablets |
|  | YY MM DD | | | | | |  |  |
| 6 |  |  |  |  |  |  | Tablets | Tablets |
|  | YY MM DD | | | | | |  |  |
| 7 |  |  |  |  |  |  | Tablets | Tablets |
|  | YY MM DD | | | | | |  |  |
| 8 |  |  |  |  |  |  | Tablets | Tablets |
|  | YY MM DD | | | | | |  |  |
| 9 |  |  |  |  |  |  | Tablets | Tablets |
|  | YY MM DD | | | | | |  |  |
| 10 |  |  |  |  |  |  | Tablets | Tablets |
|  | YY MM DD | | | | | |  |  |

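### No contact is scheduled and no adverse-event diary is kept between Day 1 and Visit 3, so non-serious GI event counts and dates rest mainly on recall over about 12 weeks

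*Protocol*

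**What the plan says.** The Synopsis sets adverse-event collection as "Adverse events: V1-V3, at every visit". Section 4.1 gives each subject one screening visit, one randomisation visit and one follow-up visit, and Section 6.1 lists no telephone call or other planned contact in between. Section 6.3.1.2 says how events are elicited: "At each visit, the subject will be asked about their health status". It also requires dates of occurrence and resolution for each event.

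The Visit 3 window is stated in two ways. The Synopsis has "Visit 3: end of study, Day 84±7 from date of randomization", while Section 6.1 has "Book visit 3: the visit should be 84 days after visit 2 (Day 84 - 87", and Appendix 1 agrees with Section 6.1.

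The record that subjects keep at home is introduced by "If you have taken the ancillary drug (Hanmi Almagate 500 mg tablet) or the rescue drug". Its columns are the date and the number of tablets of each drug.

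On monitoring, the warnings for the experimental drug (5.3.4.3) state: "Patients must be carefully monitored for signs or symptoms of GI ulcers or bleeding while on this drug". The control-drug warnings (5.3.5.3) say much the same. Section 2.9 concludes that 12-week safety is "expected to be satisfactory with careful monitoring of adverse events and vital signs".

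Sections 7.3.2 and 7.5.3 make GI adverse events (dyspepsia, diarrhoea, nausea, abdominal pain, heartburn) a secondary endpoint. It is reported as subjects affected and event frequency over 12 weeks, with a between-arm test. Discontinuation for GI events is a separate secondary endpoint.

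**The concern.** Comparing GI adverse events is a stated secondary purpose of a trial about GI tolerability. Mild or short-lived dyspepsia, nausea or diarrhoea in the first weeks is the kind of event most easily forgotten or misdated when the first planned question comes some 12 weeks after the first dose. The plan promises an event frequency and onset and resolution dates, which retrospective recall supports poorly.

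There is also a mismatch inside the protocol. The risk-benefit argument rests on careful monitoring of adverse events and vital signs, but after dosing starts both are scheduled once, at the end. On serious skin reactions to the control drug, Section 5.3.5.4 says: "In most cases, such adverse events occur within 1 month of initiation of therapy with this drug". That period ends well before the first scheduled safety question.

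**Working it through.** **1. Length of the gap.** Inputs: drug starts on Day 1 (Visit 2); Visit 3 is Day 84±7 (Synopsis) or Day 84 to 87 (Section 6.1, Appendix 1).

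- Day 84±7: 77 − 1 = 76 days to 91 − 1 = 90 days.
- Day 84 to 87: 84 − 1 = 83 days to 87 − 1 = 86 days.

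One of the three planned adverse-event collections falls after drug start. Taking one month as 30 days, the interval from the end of the first month to Visit 3 is 77 − 30 = 47 to 91 − 30 = 61 days under the wider window.

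**2. What else could capture an event in the gap.**

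| Source | Where | What it gives | Limit |
|---|---|---|---|
| Additional visit | 6.1 | May record new events | Optional; an event must first come to notice |
| Early termination visit | 4.5.1, 6.1 | Reason and all new events | Withdrawals only, when possible |
| Drug discontinuation record | 4.5.2 | Reason, situation and duration in the CRF | A subject who stops unannounced is found at Visit 3 |
| Spontaneous report or observation | 6.3.1.2 | Recorded throughout the reporting period | Mostly depends on the subject |
| SAE report | 6.3.1.4 | Within 24 hours of awareness | Serious events, once known |
| LDQ | Appendix 2 | Eight symptoms, last four weeks | At Day 84 it reaches back to Day 84 − 28 = 56, so about the first 8 weeks are outside it |
| GSRS | Appendix 3 | Items over the past 3 months | Undated recall at Visit 3; no diarrhoea item among those printed |
| Subject log | Appendix 4 | Dated antacid and rescue use | No symptom, event or study-drug field |

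Apart from investigator observation, the unscheduled routes depend on the subject coming forward. The questionnaires are structured but do not yield dated adverse events.

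**3. Effect on the GI-event comparison.** Let p1 and p2 be the true event proportions and s the share of affected subjects who are recorded, assumed equal in both arms. The expected recorded difference is s·p1 − s·p2 = s(p1 − p2). At s = 0.8, 0.6 or 0.4 the absolute difference is 80%, 60% or 40% of its true size.

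The documents give neither s nor planning values for p1 and p2, so the power figures below are illustrations only. They are exact power for Fisher's test, 53 per arm, two-sided 5%:

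| Assumed true rates | s = 1.0 | 0.8 | 0.6 | 0.4 |
|---|---|---|---|---|
| 35% vs 12% | 0.76 | 0.61 | 0.43 | 0.23 |
| 25% vs 10% | 0.44 | 0.32 | 0.21 | 0.10 |
| 25% vs 15% | 0.19 | 0.14 | 0.09 | 0.05 |
| 20% vs 12% | 0.14 | 0.10 | 0.06 | 0.03 |

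The direction is the same in every row. The starting power runs from 0.14 to 0.76 with full capture, so the table cannot say how much this trial would lose.

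**The case against.** The strongest reply is that the protocol does have ways to record events in the interval: additional visits, early termination visits, spontaneous reports and 24-hour SAE reporting. That stands. A reader might infer that nothing records adverse events between Day 1 and Visit 3, and the text does not support that.

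A reader might also infer that the discontinuation rate rests on one recall question. It does not. Section 4.5.2 requires the reason, situation and duration of every discontinuation in the case report form, Section 4.5.1 requires the reason for every withdrawal, and Section 7.5.3 uses returned product to measure compliance. What remains is the subject who stops quietly and says so only at Visit 3.

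A third tempting reading is that under-recording pushes the trial towards a non-inferiority claim. Section 7.5.2 judges non-inferiority on LDQ change alone against 0.40. GI events are secondary and tested two-sided for a difference, so missed events cannot change that decision.

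Nor can it be said that subjects are never told which signs to report. The subject information sheet is filed separately and is not shown. In 5.3.4.3 and 5.3.5.3 the sentences on patient awareness concern cardiovascular signs; the GI sentences speak of monitoring.

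Finally, the monitoring sentences in those two sections are label-style precautions that set no visit interval, and three visits in a phase 4 trial of approved doses that excludes high-risk patients is a permissible choice. That is fair. It makes this a mismatch to reconcile, not a breach. It does not answer the data-quality point, because the GI-event endpoint still needs counts and dates.

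**Conclusion.** The point holds in limited form. No contact is scheduled and no adverse-event diary is kept for 76 to 90 days on drug (83 to 86 under the narrower window). For subjects who neither make contact nor withdraw, the incidence, frequency and dates of non-serious GI adverse events rest on recall at Visit 3.

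If under-capture is proportionally equal in both arms, the absolute between-arm difference shrinks in the same proportion. Unequal capture could distort it either way. The amount cannot be computed from the documents, which give no recall sensitivity and no planning rates for GI events. The primary analysis is untouched. The change is worth making because it is cheap and improves a stated secondary endpoint and the safety record.

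**What to change.** - **Appendix 4.** Add dated columns for any new or worse symptom, with tick-boxes for the five GI events in 7.3.2 plus 'other', and for missed or stopped study drug with the reason. Subjects already receive, are taught to complete, and return this log.
- **Section 7.5.3.** State that GI events are counted from Visit 3 questioning, unscheduled reports and the log together, identically in both arms.
- **Sections 2.9, 5.3.4.3 and 5.3.5.3.** Reconcile their monitoring statements with the visit schedule. How to do so is a clinical decision for the sponsor and investigators.
- **Visit 3 window.** Reconcile the two statements in the Synopsis and in Section 6.1 with Appendix 1.

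Cost: a reprinted log, a sentence in the analysis section, slightly more diary work for subjects and more entries to code. Reported event rates will be higher in both arms, which should be kept in mind when comparing them with studies that used less intensive collection. No new visit is needed.
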